### Randomization and record keeping

Patient data, clinical status, laboratory results, and respiratory parameters will be collected on a web-based case report form (Ferrariodati, Italia). Participants will be randomized in a ratio of 1:1. Randomization will be performed by an electronic, web-based centralized, validated system.

Randomization will be stratified according to:
RI ≥ 1 and < 1 across the range between the lowest and highest PEEP tested during the PEEP trial [23] (see the “Procedures” section for details).

All original records will be archived and secured for 10 years and then destroyed according to the hospital standards concerning destruction of confidential information.

### Data monitoring

Data monitoring will be performed for quality control purposes by an independent company not involved in the study (Clinical Trial Center, Rome, Italy). Amis of monitoring will be to evaluate the study progress and to verify the accuracy of data recording.

### Statistics

All collected data will be tabulated descriptively by study group and analyzed on an intention-to-treat basis. Comparisons between groups will be performed with the chi-squared test or the Fisher’s exact test, as appropriate. Ordinal qualitative variables or non-normal quantitative variables will be compared with the Wilcoxon sum of ranks test. Quantitative normal variables will be compared with the Student *t*-test. In particular, analysis of the primary efficacy criterion will be performed with Wilcoxon-Mann-Whitney sum of ranks test.

Consistently to other published studies [22], every participant in the treatment group will be compared with every participant in the control group and assigned a score resulting from each comparison.

Mortality takes precedence over VFD60, which takes precedence over IL6AUC. Two VFD60s will be considered different for the purpose of scoring only if their difference is larger than 5 days. Similarly, two IL6AUC’s measurements will be considered different only if their difference exceeds 10% of the smaller of the two.

These individual-comparison scores are added up to obtain the cumulative score primary endpoint for each participant. Scoring system for the primary endpoint is detailed in Additional file 4.

For the purpose of the study, mechanical ventilation will be defined as: invasive mechanical ventilation with endotracheal tube or tracheostomy and noninvasive positive pressure ventilation, including continuous positive airway pressure. High flow oxygen therapy through nasal cannula or tracheostomy will not be considered as mechanical ventilation.

The assumptions and methodology used for the determination of the sample size are detailed in Additional file 5 [35]. Given the results obtained, and adopting a conservative approach in order to compensate for the small residual random variation in the numerical assessment of the sample size, it appears that a sample size of 56 subjects per arm would be sufficient to obtain 80% power in detecting a difference in the composite endpoint, at a type 1 error level of 0.05, two-tail. With an attrition rate of 15%, a total of 132 patients in two equal groups of 66 patients each should be enrolled. This corresponds to a mean of 19 patients per center.

Primary and secondary endpoints will also be analyzed in subgroups, as defined below:
∆EELV5-16/FRC ≥ 73% [18] during the PEEP trial∆EELV5-16/FRC < 73 %[23] during the PEEP trialRI ≥ 1 and < 1 across the range between the lowest and highest PEEP tested during the PEEP trialP/F ratio < 100 mmHg at study inclusionIL-6 > 400 pg/ml at study inclusion

All analyses will be performed at a 0.05 type I error level, two tail. All statistical analyses on secondary endpoints and on subgroups will be deemed to be exploratory in nature; for this reason, no correction of nominal significance levels for multiple inference will be applied.

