### Measurements

All patients intubated due to hypoxemic respiratory failure and not included will be recorded on a dedicated screening log.

Demographics will be collected at study entry. Physiological variables will be recorded at the moment of enrolment (PEEP 5), after maximum PEEP is set before the PEEP trial, 1-6-12-24-48 h after randomization, and then on a daily basis up to 60 days or ICU discharge.

Data of the ventilation management (type of ventilation, FiO_2_, tidal volume, mean airway pressure, PEEP, plateau pressure, minute ventilation, respiratory rate, esophageal end-inspiratory and end-expiratory pressures, static stress, dynamic stress and total stress, proportion of spontaneous ventilation on minute ventilation, VO_2_, VCO_2_), physiologic data (heart rate, arterial pressure, SpO_2_, end-tidal CO_2_), and results of the blood gas analyses (pH, SaO_2_, PaO_2_, PaCO_2_, SvO_2_, PvCO_2_, oxygenation index, dead space fraction) will be collected.

*Respiratory mechanics* will be recorded at the moment of enrolment (PEEP 5), at each step of the first PEEP trial, and 1-6-12-24-48 h from randomization and then on a daily basis (72-96-120…) up to 60 days or ICU discharge. End-expiratory airway pressure (PEEP_AW_) and the end-expiratory esophageal pressure (PEEP_ES_) will be recorded during a 4-s expiratory hold. End-inspiratory airway pressure (*P*plat_AW_) and end-inspiratory esophageal pressure (*P*plat_ES_) will be measured during a 1-s end inspiratory hold. Expired tidal volume (*V*_T_) will be measured as the integration of the flow-time curve during expiration.

End-expiratory airway pressure (PEEP_AW_) and the end-expiratory esophageal pressure (PEEP_ES_) will be recorded during a 4-s expiratory hold. End-inspiratory airway pressure (*P*plat_AW_) and end-inspiratory esophageal pressure (*P*plat_ES_) will be measured during a 1-s end inspiratory hold. Expired tidal volume (*V*_T_) will be measured as the integration of the flow-time curve during expiration.

Advanced respiratory mechanics parameters will be computed afterwards. Stress will be calculated any time respiratory mechanics is measured, while strain will be measured before randomization in all patients and in the intervention group any time a PEEP trial is repeated; formulas are also shown in Table 1.

**Table 1 Tab1:** Computed respiratory mechanics parameters

*Parameter*	*Formula*
Airway driving pressure	ΔP = *P*plat_aw_ − PEEP_aw_

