Transpulmonary end-inspiratory pressure	*P*plat_L_ = Plat_aw_ − *P*plat_es_
Transpulmonary end-expiratory pressure	PEEP_L_ = PEEP_aw_ − PEEP_es_
Lung driving pressure	ΔP_L_ = *P*plat_L_ − PEEP_L_
Lung plateau pressure, elastance-derived	*P*plat_L,EL_ = *P*plat_aw_ × (ΔP_L_/ΔP)
Static respiratory system compliance	Cst_RS_ = *V*_T_/ΔP
Static lung compliance	Cst_L_ = *V*_T_/ΔP_L_
Static chest wall compliance	Cst_CW_ = *V*_T_/(*P*plat_es_ − PEEP_es_)
Oxygenation-stretch index	OSI = PaO_2_/(FiO_2_ × ΔP)
Dynamic strain	Dynamic strain = *V*_T_/FRC_PEEPset_
Static strain (strain due to PEEP)	Static strain = (PEEP_volume_ − Rec_ZEEP-PEEP_)/FRC_PEEPset_
Static stress (stress due to PEEP)	Static stress = PEEP_aw_ × (ΔP_L_/ΔP)
Dynamic stress	Dynamic stress = *P*plat_aw_ × (ΔP_L_/ΔP)

The levels of *proinflammatory cytokines* (tumor necrosis factor [TNF], interleukin 6 [IL-6], and interleukin 8 [IL-8]) will be assessed from serum probes (enzyme-linked immunosorbent assay (ELISA)) of all included patients at study inclusion and 24, 48, and 72 h after randomization.

The following *scoring systems* will be calculated daily: simplified organ failure assessment score (SOFA), modified clinical pulmonary infection score (CPIS), and Richmond agitation and sedation scale (RASS). These systems and organ failure definitions used for the study purposes are reported in Additional file 2.

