### Study endpoints

The primary endpoint will be a composite clinical outcome that incorporates in-ICU mortality, 60-day ventilation-free days (VFD60), and the area under the curve of the interleukin-6 serum blood cytokine concentration (IL6AUC) during the first 72 h of observation.

Secondary endpoints will be as follows: ICU-, 90-day and in hospital mortality, 28 and 60-day ventilation-free days (VFD60), the area under the curve (AUC) of serum blood cytokines concentrations measured as stated in the study protocol; lung static, dynamic and total stress and strain after randomization; airway and lung driving and plateau pressures, compliance, compliance/PBW, dead space fraction, PaO_2_/FiO_2_ ratio, oxygenation stretch index and oxygenation index during the study treatment; and SOFA, CPIS, the incidence of complications or adverse reactions, the frequency and duration of other adjunctive therapeutic measures, transfusion requirements, the daily cumulative doses of analgesic and sedative agents, cumulative catecholamine requirements/24 h throughout the study period, frequency and duration of renal replacement therapy, the number of failing organs, and the “organ-failure-free days” within 28 days after randomization.

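### The unadjusted t and Wilcoxon tests for secondary outcomes leave the pre-randomization values and the RI stratum unused, which costs precision but not validity

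*Protocol article*

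**What the plan says.** The Statistics section assigns tests by type of variable: chi-squared or Fisher for categorical data, and two rules for the rest. "Quantitative normal variables will be compared with the Student" t-test; "Ordinal qualitative variables or non-normal quantitative variables will be compared with the Wilcoxon sum of ranks test". It mentions no baseline covariate, no stratum term and no regression model.

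The Measurements section provides the baselines: "Physiological variables will be recorded at the moment of enrolment (PEEP 5), after maximum PEEP is set before the PEEP trial". The same variables are then taken "1-6-12-24-48 h after randomization, and then on a daily basis up to 60 days or ICU discharge". Respiratory mechanics follow the same post-randomization schedule and are also recorded at enrolment. TNF, IL-6 and IL-8 are measured at inclusion and at 24, 48 and 72 h.

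The secondary endpoints include "PaO_2_/FiO_2_ ratio, oxygenation stretch index and oxygenation index during the study treatment", along with compliance and the driving and plateau pressures. Some repeated data are reduced to one value per patient: "the area under the curve (AUC) of serum blood cytokines concentrations measured as stated in the study protocol" and "the “organ-failure-free days” within 28 days after randomization".

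Randomization is stratified by RI at a cut-off of 1. Secondary and subgroup analyses are declared exploratory and are not corrected for multiplicity.

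**The concern.** A two-sample test uses only the post-randomization value. If the pre-randomization value of the same variable predicts it, between-patient variation that could have been removed stays in the error term. A chance difference between the arms at baseline also passes partly into the comparison. The RI stratum is left out in the same way, although it was considered prognostic enough to stratify on.

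The outcomes concerned are those that would explain how an EELV-guided PEEP strategy works, if it does. The Discussion describes the trial as well powered and physiological, so wide intervals on these outcomes weaken a main part of its message. The method is stated in the article and is not merely left open: a later plan that used ANCOVA would be replacing it.

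**Working it through.** **The plan's own figure.** 56 evaluable per arm with 15% attrition: 56 / 0.85 = 65.9, rounded up to 66, or 132 in total. This agrees with the Statistics section. The 56 itself rests on Additional file 5, which is not shown. It was set for the primary composite, so no secondary outcome has a stated power.

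**Inputs.** From the document: n = 56 per arm, 1:1 allocation, two-sided 0.05. Assumed, because the document gives no figure: a true difference of 0.5 SD in one continuous outcome (one value per patient) and a baseline-outcome correlation ρ of 0.3, 0.5 or 0.7.

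**Precision.** Adjusting for baseline multiplies the outcome variance by 1 − ρ². The standard error of the difference, in SD units, is √(2/56) = 0.189 unadjusted and 0.189 × √(1 − ρ²) adjusted. By normal approximation:

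- power = Φ(0.5 / SE − 1.96)
- difference detectable with 80% power = (1.96 + 0.842) × SE
- equivalent sample size factor = 1 / (1 − ρ²)

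| | Variance left | Power | Detectable difference | Sample size factor |
|---|---|---|---|---|
| Unadjusted | 1.00 | 75.4% | 0.53 SD | 1.00 |
| ρ = 0.3 | 0.91 | 79.2% | 0.51 SD | 1.10 |
| ρ = 0.5 | 0.75 | 86.3% | 0.46 SD | 1.33 |
| ρ = 0.7 | 0.51 | 95.9% | 0.38 SD | 1.96 |

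With all 66 per arm evaluable, power is 81.9% unadjusted and 85.3%, 91.3% and 98.0% adjusted.

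**Chance imbalance.** Suppose the arms differ by 0.3 SD at baseline and there is no treatment effect. The unadjusted test statistic then has mean ρ × 0.3 / 0.189 and SD √(1 − ρ²). The chance that it exceeds 1.96 in absolute value is 6.5%, 9.0% and 11.7% for ρ = 0.3, 0.5 and 0.7. At an imbalance of 0.2 SD the figures are 5.1%, 5.1% and 4.4%, so only larger imbalances matter. An imbalance of 0.3 SD or more in a given variable has probability 2 × [1 − Φ(0.3 / 0.189)] ≈ 11%. Over all possible allocations the unadjusted test keeps its 5% level.

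**Where the gain applies.**

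- Cytokine AUC: there is one value per patient and an inclusion value in both arms, so ANCOVA applies directly.
- Compliance, driving pressure and PaO₂/FiO₂: measured in both arms before and after randomization, so adjustment is possible. PaO₂/FiO₂ on PEEP 5 is capped at 150 mmHg by eligibility, which narrows its baseline spread and suggests the lower end of the ρ range.
- Plateau pressure: the control protocol fixes it at 28–30 cmH₂O, and all patients are set to that range before the PEEP trial. Little gain is to be expected.
- Strain: re-measured after randomization only in the intervention group, so no adjusted comparison of the arms can be fitted.

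**The case against.** The strongest defence has four parts.

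- **Validity and status.** Under randomization the unadjusted tests hold their level on average, and the analyses are declared exploratory. This stands, and it limits the point to precision and interpretability.
- **The correlation is assumed.** This also stands. At ρ = 0.3 the gain is under four percentage points of power, and for plateau pressure a moderate correlation is implausible by design.
- **An unshown analysis plan may settle the detail.** This stands for how the repeats are summarised. It does not stand for the tests, which the article names.
- **A mixed model over the whole schedule is unworkable.** This stands. Five early times plus days 3 to 60 make 63 occasions, and an unstructured covariance would have 63 × 64 / 2 = 2,016 parameters for 132 patients. Follow-up also ends at ICU discharge and is cut short by death, so such a model would implicitly project values beyond death. Any model must be confined to a short window.

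A reader might go further and infer that every time point will be tested separately, and then count false positives: ten variables at five times and 0.05 would give 2.5 if every null hypothesis were true. The document does not support this. It never says how the repeats enter a test, and it already reduces cytokines to an AUC and organ failure to a count of days. One test on one summary per patient fits its wording equally well.

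**Conclusion.** The point holds as one of efficiency. For quantitative secondary outcomes the article fixes tests that ignore pre-randomization values and the stratification factor, although both are collected at no extra cost. At 56 per arm and an assumed 0.5 SD effect, the plan gives up about 4, 11 or 21 percentage points of power at correlations of 0.3, 0.5 and 0.7 (75.4% against 79.2%, 86.3% and 95.9%). These figures rest on assumed values, apply to one continuous summary per patient, and neglect the small cost of estimating the covariate terms. Any further gain from the RI stratum is not quantified.

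The planned tests are not invalid, and no false-positive count can be derived from what is written. The primary endpoint, its analysis and the total of 132 are untouched. The change is worth making because it is nearly free and the outcomes concerned carry the trial's mechanistic explanation.

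**What to change.** Replace the general t/Wilcoxon rule for these outcomes as follows:

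- **Cytokines (secondary AUCs):** ANCOVA of log AUC on arm, log inclusion value and RI stratum.
- **PaO₂/FiO₂, compliance, driving pressure and similar outcomes measured in both arms:** one pre-specified per-patient summary, or the average arm effect, over the 72-hour minimum protocol period. Adjust for the enrolment value on PEEP 5 and the RI stratum, by ANCOVA or by a mixed model restricted to that window. The scheduled times there are 1, 6, 12, 24, 48 and 72 h, so even an unstructured covariance has only 6 × 7 / 2 = 21 parameters. Use a log scale where the outcome is skewed.
- **Reporting:** one adjusted difference with its 95% CI per outcome, still labelled exploratory.
- **Death and early ICU discharge:** state how patients with truncated measurements enter each summary or model.
- **Exceptions:** leave strain out of the between-arm model, and expect little benefit for plateau pressure.

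The cost is a change of wording, slightly more analysis work and reliance on model assumptions (linearity in baseline and, for a mixed model, its missing-data assumption). No additional measurement or patient is required.

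### The primary rank test is unadjusted although age and PaO2/FiO2 at PEEP 5 are known before randomisation: a valid test that forgoes a modest, nearly free gain in power

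*Protocol article*

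**What the plan says.** The protocol article, Statistics, names the primary test outright: "In particular, analysis of the primary efficacy criterion will be performed with Wilcoxon-Mann-Whitney sum of ranks test". No covariate or stratum term is attached to it. The sample size paragraph, working with a two-sided alpha of 0.05, claims that "a sample size of 56 subjects per arm would be sufficient to obtain 80% power in detecting a difference in the composite endpoint". Dropout is then allowed for: "With an attrition rate of 15%, a total of 132 patients in two equal groups of 66 patients each should be enrolled". The inputs behind the 56 are elsewhere: "The assumptions and methodology used for the determination of the sample size are detailed in Additional file 5", which is not shown.

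Three kinds of baseline information bear on the point:

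- **Age and PaO2/FiO2.** Under Measurements: "Demographics will be collected at study entry. Physiological variables will be recorded at the moment of enrolment (PEEP 5" (the quote stops inside the bracket). Age belongs to the demographics. PaO2/FiO2 at PEEP 5 is also the eligibility measurement under Oxygenation criterion validation, so each enrolled patient has it, at 150 mmHg or below.
- **RI.** Allocation is equal ("Participants will be randomized in a ratio of 1:1") and stratified on RI of at least 1 versus below 1, so this value too is known before allocation.
- **SOFA.** Measurements says only that the scoring systems "will be calculated daily: simplified organ failure assessment score (SOFA" and others. The text names no pre-randomisation value, and the SPIRIT schedule (Fig. 1) is not shown.

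PaO2/FiO2 below 100 mmHg and RI otherwise enter the analysis only as exploratory subgroups.

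**The concern.** The composite ranks patients first on ICU death, then on 60-day ventilator-free days, then on the IL-6 area under the curve. If severity at entry predicts any of these, an unadjusted test leaves that variation in its error term. In a trial of 132 patients a few points of power matter, and the covariates are collected anyway.

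Randomisation is stratified on RI alone, so chance differences in severity are left to luck. With 66 per arm, the standardised difference in a baseline covariate has SD sqrt(2/66) = 0.174. The chance that it exceeds 0.25 SD is therefore about 15%; with 56 per arm (SD 0.189) it is about 19%. Such a difference makes an observed result harder to read, and pre-specified adjustment deals with it without a later argument over which covariates to use.

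**Working it through.** **Inputs.** From Statistics: two-sided alpha 0.05, power 80% at 56 per arm, attrition 15%, 66 per arm enrolled. From Randomization and record keeping: 1:1 allocation. Not in the documents: R2, the share of variance of the ranked score that the baseline covariates explain jointly. It is an assumption, shown as a range.

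**Step 1, the plan's own figure.** 56 / (1 - 0.15) = 65.9, rounded up to 66 per arm, 132 in total. This reproduces. The 56 cannot be rebuilt without Additional file 5, so the effect is taken as whatever gives 80% power at 56 per arm. The noncentrality is 1.960 + 0.842 = 2.80, the standardised difference 2.80 x sqrt(2/56) = 0.529. In rank-test terms (Noether's formula) the win probability is 0.5 + 2.80 / sqrt(12 x 0.25 x 112) = 0.653.

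**Step 2, effect of adjustment.** Adjustment shrinks the residual SD by sqrt(1 - R2), so

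power = Phi(2.80 / sqrt(1 - R2) - 1.96), and n per arm for 80% power = 56 x (1 - R2), rounded up, then divided by 0.85 and rounded up.

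| Assumed R2 | Power at 56 per arm | n per arm for 80% | Enrolment for 80% |
|---|---|---|---|
| 0 | 80.0% | 56 | 132 |
| 0.05 | 82.0% | 54 | 128 |
| 0.10 | 84.0% | 51 | 120 |
| 0.15 | 86.0% | 48 | 114 |
| 0.20 | 87.9% | 45 | 106 |

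For R2 = 0.10: 2.80 / 0.949 = 2.95; 2.95 - 1.96 = 0.99; Phi(0.99) = 0.84.

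If all 66 per arm are evaluable, unadjusted power is already 86.0%, rising to 89.4% at R2 = 0.10 and 92.5% at R2 = 0.20.

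**Step 3, check on the three-tier score.** A simulation scored all pairs of patients on death, then ventilator-free days (margin 5 days), then IL-6 (margin 10%), with 56 per arm and control ICU mortality assumed at 35-39%. The effect was tuned so that the unadjusted test had close to 80% power. The plain test was compared with rank ANCOVA on three baseline covariates (3,000 runs per setting, 2,000 under the null).

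| R2 in simulation | Unadjusted power | Adjusted power |
|---|---|---|
| 0 | 81.4% | 80.8% |
| 0.07 | 80.3% | 83.1% |
| 0.16 | 79.0% | 84.5% |
| 0.24 | 79.2% | 88.8% |

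Adjusted type I error was 4.4-5.7% across all settings run. The formula and the simulation agree, and uninformative covariates cost 0.6 points (81.4 - 80.8).

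**Step 4, a condition on the score.** Statistics describes scoring treated patients against controls. If each patient is scored only against the opposite arm and a rank-sum test is then run on those sums, a simple null simulation (56 per arm, one continuous outcome) gave a type I error of about 27%, against 4.8% for all-pairs scoring. Additional file 4, not shown, may settle which is meant. This is a separate matter, but the figures above hold only for all-pairs scores.

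**The case against.** The strongest reply is that nothing here is wrong. An unadjusted rank test, named in advance, is a legitimate choice for a hierarchical score, and the 132 reproduces. Chance imbalance is already covered by the 5% error rate and is not bias. Adjusted analyses are often placed in a statistical analysis plan, which is not shown. Most of this stands. However, the article does not leave the primary test open; it names one, and a later plan that adjusted would depart from it.

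The second reply is that the gain is entirely assumed. That also stands. The documents give no association between any baseline variable and the outcome. Eligibility trims the spread: PaO2/FiO2 is cut at 150 mmHg, its blood gas may be drawn at any time in the 30-minute period, and patients over 85 or in intractable shock are excluded. The higher R2 values are therefore less credible than the lower ones.

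A reader might infer more than the documents support:

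- **That the trial is underpowered.** It is not shown to be; the stated 80% refers to the unadjusted test.
- **That entry severity drives the death and ventilator-free-day tiers.** This is plausible clinically, but no figure in the article backs it, and a third tier (IL-6) also contributes.
- **That SOFA is ready to use as a baseline covariate.** The text says daily, not before randomisation.

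**Conclusion.** The point holds as a missed gain in efficiency, not as an error. The primary test is fixed without covariates although age, PaO2/FiO2 at PEEP 5 and the RI stratum are known before allocation. Pre-specified adjustment would add about 2 to 8 points of power at 56 per arm for assumed R2 of 0.05 to 0.20, keep type I error near 5%, and cost under 1 point if the covariates carry no information. The size rests on the assumed R2, on an effect back-solved from the stated power, and on scores computed over all pairs. The unadjusted test remains valid.

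**What to change.** Before data lock, and preferably early because the trial is open-label, amend Statistics as follows:

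- State that the hierarchical score is computed over all pairs of patients in both arms, if that is what Additional file 4 intends. This must be clear before any adjusted version is written.
- Name a covariate-adjusted rank analysis (for example rank ANCOVA) of that score as primary, at two-sided 0.05, with age, continuous PaO2/FiO2 at PEEP 5 and the RI randomisation stratum.
- Add SOFA only if a value taken before randomisation is specified and recorded.
- Keep the unadjusted Wilcoxon-Mann-Whitney test as a sensitivity analysis.

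Adjusted models for mortality are optional, since the article treats all secondary analyses as exploratory.

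The cost is a paragraph of analysis wording plus clarification of the scoring set, with no new patients. Age, PaO2/FiO2 and RI need no new measurement. The covariates must be named in advance, and a simple rule is needed for imputing the rare missing baseline value.

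### Randomisation is stratified by RI but the primary rank-sum test is not: if RI predicts the composite, the test is conservative and gives up some power

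*Protocol article*

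**What the plan says.** Under Randomization and record keeping, the protocol article states: "Participants will be randomized in a ratio of 1:1". The only stratification factor listed is "RI ≥ 1 and < 1 across the range between the lowest and highest PEEP tested during the PEEP trial".

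Under Statistics, the primary composite (ICU death, then VFD60, then IL6AUC) is scored so that "every participant in the treatment group will be compared with every participant in the control group and assigned a score resulting from each comparison". The scores are summed per participant, and "analysis of the primary efficacy criterion will be performed with Wilcoxon-Mann-Whitney sum of ranks test". Neither the scoring nor the test refers to the RI strata. RI appears again only in the subgroup list, and the article declares subgroup analyses exploratory.

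On size, the same section says "a sample size of 56 subjects per arm would be sufficient to obtain 80% power in detecting a difference in the composite endpoint". The test level is two-sided 5%, and the number is raised to 66 per arm, 132 overall, to allow for 15% attrition. The effect size and outcome distributions are not in the article: "The assumptions and methodology used for the determination of the sample size are detailed in Additional file 5", which is not shown. Additional file 4, which holds the scoring details, is not shown either.

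**The concern.** Stratified allocation forces the two arms to have nearly the same mix of RI ≥ 1 and RI < 1 patients. If the two strata have different outcomes, part of the spread in the scores can then no longer fall unevenly between the arms. The unstratified rank-sum variance still counts that part as noise. The test statistic therefore varies less than its reference distribution supposes, so the test rejects too rarely under the null and loses power under the alternative.

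This is more than a detail left to the SAP, because the article itself names the test and an all-pairs scoring rule. At stake is efficiency in a small trial, 56 evaluable patients per arm. Validity is not at stake on this point.

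**Working it through.** **The plan's own figure.** 56 / 0.85 = 65.9, so 66 per arm and 132 in total. This reproduces the article. The 56 itself cannot be rebuilt, because its assumptions are in Additional file 5.

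**Implied effect.** Noether's formula for the rank-sum test with N = 112, two-sided 0.05 and 80% power gives P(X>Y) = 0.5 + (1.960 + 0.842)/√(12 × 0.25 × 112) = 0.5 + 2.802/18.33 = 0.653. On a normal scale this is a shift of about 0.55 SD.

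**Expected conservatism.** Let R² be the share of score variance explained by the stratum. With strata of equal size and a stratum difference of g SD, R² = 0.25g²/(1 + 0.25g²). Under stratified allocation the null SD of the unstratified z is about √(1 − R²), so the true alpha is about 2Φ(−1.96/√(1 − R²)). For g = 1.0, R² = 0.25/1.25 = 0.20; 1.96/√0.80 = 2.19; alpha ≈ 2.8%.

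**Simulation 1: normal stand-in for the score.** N = 112, half the patients in each stratum (assumed), permuted blocks of 4 (assumed), within-stratum effect 0.545 SD, 10,000 runs per setting. Monte Carlo SE is about 0.2 points for alpha and 0.4 for power.

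| Stratum difference (assumed) | R² | Alpha by formula | Alpha, unstratified / van Elteren | Power, unstratified / van Elteren |
|---|---|---|---|---|
| 0 | 0% | 5.0% | 4.9% / 4.8% | 80.1% / 79.4% |
| 0.3 SD | 2% | 4.8% | 4.8% / 5.0% | 79.2% / 79.6% |
| 0.5 SD | 6% | 4.3% | 4.0% / 4.6% | 77.6% / 79.0% |
| 0.8 SD | 14% | 3.5% | 3.4% / 5.1% | 75.3% / 79.6% |
| 1.0 SD | 20% | 2.8% | 3.0% / 5.3% | 72.8% / 79.9% |

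Putting 30% of patients in one stratum gives a similar pattern.

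**Simulation 2: the hierarchical composite.** 56 per arm, scores pooled over all patients, stratum gap expressed as a difference in ICU mortality. Outcome distributions are assumed and differ between the three sets. Entries are unstratified alpha, then the power gained by stratifying.

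| ICU-mortality gap (assumed) | Set A | Set B | Set C |
|---|---|---|---|
| 0 points | 4.4%, about 0 | 4.9%, 0.0 | not run |
| 10 points | 4.7%, about +1 | not run | not run |
| 15 points | 4.7%, about +1.5 | 4.3%, +0.6 | 4.5%, +2.5 |
| 25 points | 3.9%, about +3 | 3.7%, +2.5 | 3.4%, +5.3 |
| 35 points | 2.4%, about +7 | 3.3%, +5.8 | 2.3%, +9.0 |

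Set B (4,000 trials per setting) was calibrated to about 80% power. Set C (2,000 trials) had an unstratified power of only 63 to 65%, so its larger gains carry less weight. At 15 points the drop in alpha is close to simulation error.

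**Is the 80% missed?** That depends on how the 56 was derived. If it came from the pooled outcome distribution, the normal simulation with the effect rescaled to that distribution gives 80.5 to 81.7% for the unstratified test and 80 to 87.5% for van Elteren. The planned power is then met, and the loss is forgone gain.

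**The case against.** **RI may not be prognostic.** The article never says RI predicts the composite. Its Background and Discussion present recruitability mainly as a modifier of the response to PEEP, which is a different property. This objection stands and makes every figure above conditional. The article's rationale does lend some plausibility: it holds that high PEEP can harm poorly recruitable lungs, and the control arm targets one plateau range in all patients, so low-RI and high-RI controls might well differ. That supports a difference under the trial's hypothesis. It neither gives its size nor establishes one under the null.

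**The trial is underpowered or its inference is wrong.** A reader might infer this, but the documents do not support it. The error from ignoring the strata is on the conservative side, and the derivation of the 56 per arm is not shown.

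**The error bars are too wide whatever the data.** This is also a tempting inference. It fails when RI is weakly prognostic: at 0.3 SD or less the two tests are practically the same.

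**Comparing patients across strata is a flaw.** It is not one in itself. Any unadjusted randomised comparison contains such pairs.

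**Conservatism presupposes valid scores.** Taken literally, the article scores each patient only against the opposite arm. A plain rank-sum test on those scores was not conservative in simulation: it rejected about 28 to 30% of the time under the null at small stratum gaps, and about 19% at 35 points. Additional file 4 may specify pooled scoring, so this cannot be asserted as the plan. It is a separate question and a condition on this point.

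**The SAP may stratify.** It may, but the article fixes a plain test and all-pairs scoring, and a SAP that follows this text would be unstratified.

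**Conclusion.** The point holds in conditional form. The article stratifies randomisation by RI and fixes a primary test that does not use the strata. If RI is prognostic and scores are pooled validly, the test is conservative and less efficient. The loss is essentially nil for a weak association. It is roughly 1 to 7 power points for an assumed ICU-mortality gap of 15 to 35 points, with true alpha moving from just under 5% at the lower end to about 4% at 25 points and about 2.5% at 35.

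These sizes rest on assumed stratum shares, outcome distributions and prognostic strength, none of which the article gives. Severity is modest and confidence moderate: the mechanism is certain, but its size in this trial is unknown.

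**What to change.** Pre-specify a stratified primary test. Score pairs only within RI stratum and combine the two strata by van Elteren (stratum weights 1/(N_k + 1)) or a stratified Finkelstein-Schoenfeld test. Report the unstratified result as a sensitivity analysis.

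The cost is a short change of text. RI is measured before randomisation, and patients whose EELV cannot be measured are not randomised, so the stratum should be known for everyone. The sample size stays at 132.

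There are three trade-offs to accept openly:
- Cross-stratum pairs are no longer used.
- If RI is not prognostic, power is at most negligibly lower (79.4% against 80.1% in simulation 1; no difference in set B).
- The quantity estimated becomes a stratum-weighted effect, which differs from the overall one if RI modifies the treatment effect. The chosen weights should therefore be stated.
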